### Recruitment, Randomization, and Procedures

Research sites will be recruited through a partnership with local communities, personal contacts, referrals, and phone calls. The unit of randomization is an independent living senior community, which is defined as a company-owned facility with a design for low-income independent adults aged ≥55 years and without health care services provided on campus. Research sites will be selected based on the prespecified criteria, including the number of residents, geographic proximity (urban vs suburban), and ability to implement the intervention. We plan to recruit 6 sites (3 intervention sites and 3 control sites). Collectively, approximately 10 sites and 800 low-income individuals are available for screening, and we can add sites, as they are abundant in the area. The participating sites will be randomized to either the intervention or control group in a 1:1 ratio. RX (coinvestigator and statistician) will use a computerized pseudorandom number generator to determine the randomization order in advance. The project director (PD) will reveal the randomization of the sites before the study [57]. Following randomization, we will recruit participants using standard strategies, including placing flyers on information boards and participating in open-house sessions or health fairs for face-to-face recruitment. Participants will also be recruited from their units by email. We will screen participants by a phone call to determine their initial eligibility, and those eligible will be invited for the baseline assessment. The research staff will explain the study and complete the consent process. The PEER intervention sites will be required to select 6 to 7 volunteers called *peer coaches* (PCs) to lead the exercise group, and the PCs will be eligible if they report having a regular PA routine or having an educational background in health care; are aged >55 years; can read, write, and understand English and Spanish; and are committed to delivering the protocol for 8 weeks. JS (coinvestigator) and the principal investigator (PI) will provide two, 3-hour sessions to train the PCs in balance and strength training, safety in the exercise, and participant motivation in collaboration with a successful PC from our pilot study. Each PC will be matched to 8 to 10 low-income older adults in the PEER group according to the place of residence and will supervise low-income older adults in groups while they are engaged in group exercises. This procedure was successful in our pilot study.

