#### Step 3: Peer-Led Exercises

*Peer-led exercises* focus on balance, strength training, and incorporating exercises into daily activities. A trained PC will lead the group-based exercises for 60 minutes (8-10 per group). Exercise training includes 4 sets of warm-ups, strength for the upper and lower body, balance (standing and moving), and stretching of the upper and lower body. Our training sessions follow the guidelines established by the American College of Sports Medicine, which take into account the frequency, intensity, time, and type of exercise recommended for each individual level of progression. These levels are classified as beginner, intermediate, and advanced [58,59]. On the basis of these guidelines, a duration of 91 to 120 minutes of exercise per week is the most effective in improving overall balance performance [60]. Therefore, the dose of exercise that will be tested in the PEER group is 120 minutes for 8 weeks (60 min/wk for group exercise led by the peer and at least 30 min twice a wk for individual exercise). We will offer a booklet with exercise instructions in both English and Spanish, featuring illustrations to guide users through each exercise set. The booklet contains a diverse range of exercises that can be easily incorporated into daily routines, such as cooking. The participants will be instructed to keep a weekly log of their exercise activities, noting the type and duration of each activity they performed at home.

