### Control Group

The control group or enhanced usual care will receive an information pamphlet about falls (English or Spanish version) developed by the CDC Stopping Elderly Accidents, Deaths, and Injuries–Older Adult Fall Prevention. These pamphlets provide details on fall risk, ways to prevent falls, how to check for safety, postural hypotension, chair rise exercise, what they can do to avoid falls, ensure safety, and manage postural hypotension [2]. The control group will be encouraged to discuss fall prevention with their primary care provider and continue their regular activities for 6 months. They will be offered the PEER intervention when the study concludes. They will receive monthly phone calls from the RA to record a monthly fall incidence log.

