### Data Analysis

We will collect demographic information from the participants for the study. We will compare baseline variables, such as essential participant characteristics, primary, and secondary end points, to summarize the differences between the 2 groups at the start of the study (T1). For the analysis of categorical data and continuous data, the chi-square test and 2-tailed *t* test will be used. We use R (version 4.1.2; R Foundation) for data analyses, with a significance level of *P*=.05.

Aim 1 is to examine the effects of the technology-based PEER intervention on fall risk, dynamic balance, and accelerometer-based PA.

The hypotheses are as follows:

*H 1.1*: The PEER group will reduce the fall risk compared with the control group.*H 1.2*: The PEER group will improve the dynamic balance compared with the control group.*H 1.3*: The PEER group will improve accelerometer-based PA compared with the control group.

Data will be analyzed according to the intention-to-treat principle [100]. We will model the fall risk, dynamic balance, and accelerometer-based PA as longitudinal outcomes consisting of 4 measurements (baseline or T1, after program completion or T2, follow-up at 3 months or T3, and follow-up at 6 months or T4) using the longitudinal linear mixed model (LMM) [101]. The LMM allows all low-income older adults and their available data to be included in the analysis, even for unequal group sample sizes, and the group heterogeneity can be addressed in the variance structure of random effects. It is hypothesized that the PEER group will show improvement in all outcome measures over time. To test hypothesis *1.1*, between-arm differences for fall risk scores, the likelihood ratio test (LRT) [101] associated with LMM will be used from all follow-up assessment visits. Similarly, the LRTs will be used to test hypotheses *1.2* and *1.3* for between-arm differences for dynamic balance and PA, respectively. The CDC-recommended scoring scheme will be adopted to process fall risk, TUG, and STS data [102]. For example, the average score of the number of STS repetitions a person can complete is based on different age and sex groups [102].

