*H 2.1*: The PEER group will have a more adaptive shifting compared with the control group.*H 2.2*: The PEER group will have a more positive shift in their perceptions of aging compared with the control group.

To test hypothesis *2.1* (FRA shifting), the 4 FRA quadrants will be determined by grid coordinates based on 2 continuous level measures (BBS and short FES-I scores). We will classify shifting into 2 types: maladaptive and adaptive shifting. Adaptive shifting is moving from irrational, incongruent, or congruent to rational. The outcome is a percentage of low-income older adults with baseline (T1) in irrational, incongruent, or congruent quadrants who end up in the rational quadrant after program completion (T2). Maladaptive shifting is a movement from rational to any other quadrant, and the percentage of low-income older adults will be calculated. After program completion (T2), the baseline FRA categories (T1) may remain the same or shift to a different FRA category. We will form a 4×4 contingency table for the 4 FRA categories at each follow-up time point (T3 and T4) to summarize the shifts. The standard 4×4 table analysis will be performed to examine the FRA shifting, either using a chi-square test or exact test, depending on the actual counts observed in the 4×4 table. The BBS and short FES-I scores will be collected in 4 planned visit time points (T1, T2, T3, and T3). We will use the Generalized Linear Mixed Model (GLMM) to analyze these 2 end points for assessing the difference between the PEER intervention and control arms on the shift of FRA categories [109]. Our longitudinal data on the PEER effects of different types of shifting on low-income older adults will contain repeated binary measures of the shifting status over time. The binomial GLMM with the logic link will allow us to assess the difference between the 2 arms in FRA shifting, and the associated LRT [101] will be used to test hypothesis *2.1* if a significant adaptive shifting is detected in the PEER group compared with the control group. The GLMM can address the group heterogeneity by specifying the corresponding covariance structure in random effect terms.

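### Peer-coach groups exist only in the PEER arm, yet the described models name neither a coach-group nor a site level; site-level inference is needed first, with a PEER-only coach term as a second level

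*Protocol article*

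**What the plan says.** Sites are randomised: "The unit of randomization is an independent living senior community", and "We plan to recruit 6 sites (3 intervention sites and 3 control sites" (Protocol article, Recruitment, Randomization, and Procedures).

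Below the site, only the PEER arm has a further level. "The PEER intervention sites will be required to select 6 to 7 volunteers called *peer coaches* (PCs) to lead the exercise group", and then "Each PC will be matched to 8 to 10 low-income older adults in the PEER group according to the place of residence". Step 3 of the Intervention section agrees: "A trained PC will lead the group-based exercises for 60 minutes (8-10 per group". Coaches also make the adherence calls (Treatment Fidelity and Monitoring). Controls have no counterpart: "The control group or enhanced usual care will receive an information pamphlet about falls (English or Spanish version", plus monthly calls from a research assistant (Control Group).

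The Data Analysis section plans a longitudinal LMM with likelihood ratio tests for H1.1 to H1.3, a binomial GLMM with a likelihood ratio test for H2.1, and a mixed-model ANOVA for H2.2. On random effects, the LMM text says that "the group heterogeneity can be addressed in the variance structure of random effects". The GLMM text says: "The GLMM can address the group heterogeneity by specifying the corresponding covariance structure in random effect terms". Neither says what a group is, and the ANOVA text names no level at all. Power Analysis and Sample Size gives one ICC, 0.8, beside repeated measures, and no design effect for sites or coach groups.

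**The concern.** People who share a volunteer coach, a weekly exercise group and a place of residence are likely to have correlated outcomes. This correlation comes from delivery and exists in one arm only, so the design is partially nested. A model that sees only participants and their repeated visits misses it, understates the PEER-arm variance, gives intervals that are too narrow and rejects too often.

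The word *group* does not settle the matter. In the LMM paragraph it follows a remark on unequal group sizes, and the section calls the arms groups throughout, so the arms are the natural reading. Elsewhere the article also uses the word for exercise groups. An analyst could follow the text and fit no term for coach or site.

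**Working it through.** **The plan's own figure.** The article gives no coach-level figure to reproduce. Its secondary statement (120 per arm, 80% power, d = 0.36) does reproduce: (1.96 + 0.842) × √(2/120) = 0.362. That formula takes all participants as independent, so the figure contains no allowance for sites or coaches.

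**Inputs.** From the article: 170 enrolled and 120 completing per arm, 3 PEER sites, 6 to 7 coaches per PEER site, 8 to 10 participants per coach. Coach and site ICCs are not given. I assume 0.02, 0.05 and 0.10 for coach, and 0, 0.02 and 0.05 for site.

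**Step 1: group size.** 3 × 6 = 18 coaches; 170/18 = 9.44 enrolled per group; 120/18 = 6.67 completers per group.

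**Step 2: no site variance, participants taken as independent.** PEER-arm design effect DE = 1 + (m − 1) × ICC; control DE = 1. SE ratio of the arm difference = √((DE + 1)/2). True level = 2 × (1 − Φ(1.96/SE ratio)).

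| Coach ICC | DE (m = 9.44) | SE ratio | True level | True level, completers (m = 6.67) |
|---|---|---|---|---|
| 0.02 | 1.17 | 1.04 | 6.0% | 5.7% |
| 0.05 | 1.42 | 1.10 | 7.5% | 6.7% |
| 0.10 | 1.84 | 1.19 | 10.0% | 8.4% |

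At the stated limits of group size, the true level is 5.8/7.1/9.2% for groups of 8 and 6.0/7.7/10.4% for groups of 10.

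**Step 3: the site level, for scale.** 170/3 = 56.7 per site in both arms. At site ICC 0.02, DE = 1 + 55.7 × 0.02 = 2.11, against 1.17 for coach groups at the same ICC. The true level is then about 17.8% if site is ignored.

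**Step 4: both levels together.** Simulation under no effect: 6,000 trials per row, 3 + 3 sites, 6 coach groups of 9 per PEER site, one outcome per participant. Rejection rates at nominal 5%:

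| Site ICC | Coach ICC | Participants independent | Coach term, no site term | Site intercept, no coach term, normal reference | Site means, t on 4 df |
|---|---|---|---|---|---|
| 0 | 0 | 5.2% | 4.6% | 4.2% | 5.5% |
| 0 | 0.02 | 6.2% | 5.2% | 4.3% | 5.1% |
| 0 | 0.05 | 7.3% | 5.3% | 5.1% | 5.4% |
| 0 | 0.10 | 9.5% | 5.5% | 5.9% | 4.8% |
| 0.02 | 0 | 18.0% | 16.0% | 9.2% | 4.9% |
| 0.02 | 0.05 | 18.6% | 14.3% | 9.3% | 5.4% |
| 0.02 | 0.10 | 21.5% | 14.2% | 9.5% | 4.9% |
| 0.05 | 0.05 | 33.1% | 26.5% | 11.9% | 5.6% |
| 0.05 | 0.10 | 32.9% | 23.8% | 10.9% | 5.0% |

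Monte Carlo error is about 0.3 points at 5% (√(0.05 × 0.95/6000) = 0.0028).

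**Step 5: reading the table.** The first row of the third column agrees with the formula within simulation error, as do the rows below it. With a site intercept, going from no coach effect to a coach ICC of 0.10 adds 1.7 points at site ICC 0 and 0.3 at site ICC 0.02. Separate runs of the same layout gave 3.8% to 6.4% at site ICC 0, and 6.4% to 8.6% at site ICC 0.01. The added inflation is therefore about 0 to 2.5 points. A coach term without a site term leaves the test badly inflated once sites differ. Site and coach terms together with a normal reference still gave about 8% at site ICC 0.02.

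**The case against.** Four arguments stand against the point.

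*The plan does not say that participants are independent.* This stands. A reader might infer that PEER participants sharing a coach are treated as independent, but the article calls the trial clustered and mentions random effects in both main models. Independence is one possible result of ambiguous wording.

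*Coach groups lie inside the randomised sites, so a site-level analysis already carries their variance.* This also stands. A reader might infer that the 6.0/7.5/10.0% applies whatever else is in the model. It applies only if the site term is missing too. Site means on 4 df stay near 5% throughout.

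*Random-effects structure is usually left to an analysis plan.* This stands in part, since silence alone would be no finding. Here, however, the article does say what the random effects are for, in a word that could mean arm, site or exercise group, and it commits to likelihood ratio tests with six randomised units.

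*The coach ICC is assumed.* True. At 0.02 the test is at about 6% even with no site term.

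A reader might also infer that coach quality can never be separated from the programme. The article does not support that: it plans a process evaluation, and its matching of coaches to participants creates the information needed.

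**Conclusion.** The point holds in a limited form. The described models name neither level of clustering, and the one relevant phrase is ambiguous. If participant-level random effects are all that is fitted, a nominal 5% test runs at about 6.0/7.5/10.0% for coach ICCs of 0.02/0.05/0.10 without site variance, and at about 18 to 22% with a site ICC of 0.02.

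The coach level is the smaller part of this. The documents do not support the stronger reading that a missing coach term is by itself what invalidates the test, or that adding one would repair it. Valid inference on the arm effect depends on the site effect and its small-sample reference distribution. The coach term describes the PEER arm properly and gives an ICC of practical use.

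These figures rest on assumed ICCs, equal group sizes, 18 coaches and one outcome per participant. The model columns use a normal reference as a stand-in for the likelihood ratio test.

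**What to change.** In Data Analysis:

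1. Say what *group* means in the LMM and GLMM paragraphs, and list the random effects for all three models, including the mixed-model ANOVA.
2. Include a site random effect, and replace the asymptotic likelihood ratio test of the arm effect with small-sample inference for 3 + 3 sites: t with about 4 df or Kenward-Roger for the LMM, and a site-level summary analysis for the binary shifting outcome. A permutation test is also valid, but six sites allow only 20 allocations, so its smallest two-sided P value is 2/20 = 0.10. It becomes usable at 5% with four sites per arm (70 allocations, 2/70 = 0.029); the article says that sites can be added.
3. Add a coach-group random intercept for PEER participants only, nested in site, with controls as singletons and arm-specific residual variance, as a second level or supporting analysis. If the arm contrast is made on site summaries, state that these carry the coach variance.
4. Keep the coach ID in the analysis data set and report the coach ICC.

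The cost is a few sentences and one ID variable that the matching already creates. Enrolment was still under way at publication, so the ID should be easy to retain. The statistical cost is wider intervals: for the same standard error, t on 4 df (2.776) in place of 1.96 widens them by 2.776/1.96 = 1.42. The coach term itself adds little to that.

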
### Intervention

The PEER consists of 3 components with 3 steps.

#### Step 1: Technology-Based Physio-Feedback

The research assistant (RA) presents the BTrackS software (Balance Tracking Systems, Inc) to display the participant’s BBS scores with interpretations and then categorizes the participants into 4 groups (irrational, incongruent, congruent, and rational) according to the FRA matrix and plots the position in 1 of the 4 quadrants on the FRA matrix chart (Figure 1). The RA will provide physio-feedback to the participants at baseline (T1) and after program completion (T2).

**Figure 1 figure1:**
[figure not shown]
Technology-based physio-feedback. CDC: Centers for Disease Control and Prevention; FRA: fall risk appraisal.

#### Step 2: Cognitive Reframing

*Cognitive reframing* will be based on the FRA matrix. We will present the FRA matrix, and activities will be tailored based on the quadrant that the participant fits (Figure 1):

*Quadrant 1* (irrational): focus on increasing balance confidence and maintaining exercise.*Quadrant 2* (incongruent): focus on individual fall risk factors from the CDC fall risk checklist, enhance fall risk awareness, and participate in the exercise.*Quadrant 3* (congruent): focus on individual fall risk factors from the CDC fall checklist and participate in the exercise.*Quadrant 4* (rational): encourage to maintain exercise.

#### Step 3: Peer-Led Exercises

*Peer-led exercises* focus on balance, strength training, and incorporating exercises into daily activities. A trained PC will lead the group-based exercises for 60 minutes (8-10 per group). Exercise training includes 4 sets of warm-ups, strength for the upper and lower body, balance (standing and moving), and stretching of the upper and lower body. Our training sessions follow the guidelines established by the American College of Sports Medicine, which take into account the frequency, intensity, time, and type of exercise recommended for each individual level of progression. These levels are classified as beginner, intermediate, and advanced [58,59]. On the basis of these guidelines, a duration of 91 to 120 minutes of exercise per week is the most effective in improving overall balance performance [60]. Therefore, the dose of exercise that will be tested in the PEER group is 120 minutes for 8 weeks (60 min/wk for group exercise led by the peer and at least 30 min twice a wk for individual exercise). We will offer a booklet with exercise instructions in both English and Spanish, featuring illustrations to guide users through each exercise set. The booklet contains a diverse range of exercises that can be easily incorporated into daily routines, such as cooking. The participants will be instructed to keep a weekly log of their exercise activities, noting the type and duration of each activity they performed at home.

### Treatment Fidelity and Monitoring

The PI and PD will oversee the treatment fidelity and monitoring plan. We will use a modified Treatment Fidelity Assessment Tool based on National Institutes of Health’s Behavioral Change Consortium treatment fidelity research [61]. In total, 5% (17/340) of the intervention sessions will be randomly observed by the PI using the modified Treatment Fidelity Assessment Tool, including treatment design, training, delivery of treatment, receipt of treatment, and enactment of treatment skills [61,62]. It is evaluated on a 3-point scale (1=present, 2=absent but should be present, and 3=not applicable). Problems identified, including deviation from the protocol, will be discussed with the research team, assessors, and interventionists biweekly. Retraining will be provided if adherence is <90%. A continual process evaluation plan will be used in this study. The plan is based on the guidelines of the Medical Research Council framework [63], which includes three components: (1) implementation, (2) mechanisms of impact, and (3) contextual factors. The implementation of the PEER intervention will be evaluated based on fidelity (whether the PEER was delivered as intended), completeness (quantity of the PEER implemented), adaptation (alterations made), and reach (characteristics of the population reached). The mechanisms of impact (how the delivered PEER produced change) and contextual factors (how context affects implementation and outcomes) will be assessed in this study. Adherence to the PEER intervention will be monitored by phone calls by a PC. Adverse events will be monitored throughout the study period. Low-income older adults will be instructed to contact RAs, the PI, or the PD if they have falls, near falls, or a change in status that led to medical attention. Contact will be recorded by the RAs. The low-income older adults will be asked to identify reasons for adherence as well as nonadherence. A project logbook, registration checklists, participant records, and self-reports will be used to collect these data.

### End Points

The intervention will be delivered per protocol until 1 of the following end points is met (whichever occurs first): (1) unable to participate in PEER activities (eg, exercise), (2) past 8 weeks of enrollment, and (3) other exclusion criteria are met (eg, severe cognitive problems).

### Control Group

The control group or enhanced usual care will receive an information pamphlet about falls (English or Spanish version) developed by the CDC Stopping Elderly Accidents, Deaths, and Injuries–Older Adult Fall Prevention. These pamphlets provide details on fall risk, ways to prevent falls, how to check for safety, postural hypotension, chair rise exercise, what they can do to avoid falls, ensure safety, and manage postural hypotension [2]. The control group will be encouraged to discuss fall prevention with their primary care provider and continue their regular activities for 6 months. They will be offered the PEER intervention when the study concludes. They will receive monthly phone calls from the RA to record a monthly fall incidence log.

